### Control

As the aim of the trial is to compare the effectiveness of the exercise program with routine care, the control group is a routine care control group. This means that study participants will receive routine care according to national guidelines [22], which does not involve a standardised, structured exercise program, but may include information and advice about physical activity from the treating nurse, physician or physiotherapist.

At the completion of the trial, following the 6-month post-baseline (follow-up) testing session, the study participants in the control group will be offered a home exercise program, a written PAP, and the same exercise information booklet the exercise intervention group was given. In addition, they will also be offered a hard copy of the same exercise program used in the intervention, including pictures and instructions for the exercises.

### Outcomes

Participants will complete measurements for primary and secondary endpoints at baseline, 3 months post-baseline (post-intervention), and 6 months post-baseline (follow-up) (Table 1). Participants will attend the exercise lab at the Karolinska Comprehensive Cancer Centre for the testing sessions and questionnaires will be completed online.

#### Primary outcome

The primary endpoint, patient-reported HRQoL at 3 months (post-intervention), will be assessed using the European Organization for Research and Treatment of Cancer quality of life questionnaire (EORTC QLQ-C30), a cancer-specific instrument that measures HRQoL in relation to physical, emotional, social, cognitive, and everyday function [23, 24].

#### Secondary outcomes

Estimated CRF (estimated/predicted maximal oxygen uptake, VO_2_max) assessed by the Ekblom-Bak submaximal cycle test [25, 26] on a cycle ergometer (Monark 928E, Monark Exercise AB, Sweden).Muscle strength assessed by the hypothetical 1 repetition maximum (1-RM) test for both the upper body (chest press) and lower body (leg press) [27]. Additionally, handgrip strength [28] assessed using a hydraulic hand dynamometer (SAEHAN Corporation, South Korea).Physical function assessed by the 5 sit-to-stand test, where participants will be asked to stand up and sit down in a chair as fast as they safely can five times [29].Body composition measured using bio-impedance analysis (BIA) to assess body fat (BF%), fat mass (kg) and lean mass (kg), using the (InBody770, InBody Corporation, South Korea).Common cancer-related symptoms assessed by the 32-item Memorial Symptom Assessment Scale (MSAS) including occurrence, frequency, severity, and distress associated with each symptom using four- and five-point rating scales [30]. The instrument has been validated for Swedish patients with breast cancer [31].Fatigue assessed by the Piper Fatigue Scale including the four dimensions of behavioural/severity, affective meaning, sensory, and cognitive/mood [32]. The instrument has been shown to be reliable among Swedish populations of patients with cancer [33].Self-reported physical activity assessed by the Modified Godin Leisure Time Physical activity questionnaire [34].Patient-reported HRQoL will be also measured at the follow-up timepoint as a secondary endpoint.Self-efficacy for exercise (SEE) assessed by the Self-Efficacy of Exercise questionnaire [35] – Swedish version (SEE-SV) [36, 37] to examine whether SEE is a predictor of short and long-term changes in exercise behaviour in this trial.

Attendance and adherence to the exercise sessions will be continuously reported by the personal trainer to the research team. Additionally, cost-effectiveness will be measured using the EuroQol 5 Dimension 5 Level (EQ-5L-5D) questionnaire [38] and purpose-designed cost-effectiveness and willingness to pay questionnaires.

To explore and describe the experiences of participation in the exercise program, the participants in the intervention group will complete a purpose-designed questionnaire. Furthermore, a selection of the participants from the intervention group and the personal trainers involved in delivering the exercise program will be invited to participate in separate focus groups or individual interviews.

Participant demographics including general medical and cancer history, resting heart rate, resting blood pressure, body mass, height, body mass index, age, sex, smoking status, education level, relationship status, and percentage of sick leave will be recorded to characterise the participant groups.

### Participant timeline

Following screening and providing informed consent, participants will answer questionnaires online and complete baseline testing at the exercise lab (Table 1 and Fig. 1). Following the baseline testing session participants will be randomised to either the intervention group or routine care control group. The intervention group will commence the exercise program within 2 weeks of baseline testing. The control group will continue to receive usual care and will have no contact with the research team until the 3-month testing session, unless initiated by the participant. Participants in both groups will answer questionnaires and complete testing sessions again at 3 months post-baseline (post-intervention) and 6 months post-baseline (follow-up). There will be no contact with the research team for either group between the 3- and 6-month post-baseline unless initiated by the participant.

### Sample size

We aim to include 200 participants in this trial. Sample size calculations have been based on having sufficient power to detect a medium effect size (Cohen’s *d* = 0.5) for the primary endpoint, overall patient-reported HRQoL post-intervention. We regard an improvement in HRQoL in the intervention arm from baseline to three months post-baseline relative to the control arm to be of relevance. With a power of 80% and an alpha of 5% (two tailed) from pre- to post-intervention, a total of 160 participants needs to be included; 80 in each arm.

To ensure sufficient participant numbers at the completion of the trial, sample size calculations account for a 20% attrition rate, leading to a total sample size of 200 participants.

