### Assignment of interventions

After the completion of baseline testing, study participants will be randomised by a member of the research team on a 1:1 basis in block samples, using the computer-generated randomisation program ALEA. Randomisation will be stratified by disease type (breast, prostate or colorectal) and treatment with chemotherapy (yes or no). Study investigators and participants will be blinded to group allocation at baseline, but not at the subsequent testing timepoints. The design is open label so unblinding will not occur.

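### The stated inputs (d = 0.5, 80% power, two-sided 5%) require 128 evaluable participants, not the 160 printed as the number before attrition

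*Protocol article*

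**What the plan says.** The Sample size section of the protocol article gives a full set of inputs for a two-group comparison. The effect is fixed by the phrase "sufficient power to detect a medium effect size (Cohen’s *d* = 0.5", and the error rates by "With a power of 80% and an alpha of 5% (two tailed". The target is "the primary endpoint, overall patient-reported HRQoL post-intervention", understood as intervention relative to control. Under Assignment of interventions, participants are randomised "on a 1:1 basis in block samples".

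From these inputs the article concludes that "a total of 160 participants needs to be included; 80 in each arm". A separate paragraph then says that "sample size calculations account for a 20% attrition rate, leading to a total sample size of 200 participants". Read in order, 160 is the number needed before attrition and 200 the number after it. The section states no baseline to follow-up correlation, clustering allowance, multiplicity adjustment or other reason for a larger number.

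**The concern.** The combination d = 0.5, 80% power and two-sided 5% has a well-known answer of 64 per arm, and the article prints 80. A gap of 16 per arm is too large to come from rounding or from the choice between a normal and a t formula.

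This paragraph tells readers why the enrolment target is what it is and what size of effect the trial could detect. Someone interpreting a null or borderline result would take the trial to have 80% power at d = 0.5 after 20% loss. If 160 people complete, the power is higher than that, or equivalently the trial has 80% power for a smaller effect than the one stated.

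**Working it through.** **Inputs.** d = 0.5, power 80%, two-sided alpha 5% and attrition 20% (Sample size); 1:1 allocation (Assignment of interventions).

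**Step 1: the article's own figures.** The second step reproduces: 160 / (1 − 0.20) = 200. The first step, from the inputs to 160, does not.

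**Step 2: the evaluable number from the stated inputs.**
- Normal approximation: n per arm = 2(z₀.₉₇₅ + z₀.₈₀)² / d² = 2(1.960 + 0.842)² / 0.25 = 2 × 7.849 / 0.25 = 62.8, so 63 per arm, 126 in total.
- Noncentral t: n per arm = 63.77, so 64 per arm, 128 in total (power at 64 per arm: 80.1%).
- Ratio of printed to required: 160 / 128 = 1.25.

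**Step 3: attrition applied once.** 128 / 0.8 = 160 enrolled, 80 per arm. Starting from 126, it is 157.5, rounded up to 158.

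**Step 4: what the printed numbers deliver.**
- 200 enrolled with 20% loss leaves 160 completers, 80 per arm.
- Power at 80 per arm, d = 0.5: d√(n/2) = 0.5 × √40 = 3.162; 3.162 − 1.960 = 1.202; Φ(1.202) = 88.5%. The noncentral t value is 88.2%.
- Effect detectable with 80% power at 80 per arm: d = 0.446 (noncentral t).
- Loss that 200 enrolled can absorb before falling to 128: 1 − 128/200 = 36%.

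**Step 5: does another reading give 160?** Total evaluable N at d = 0.5, and 80% power unless shown otherwise:

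| Variant | Total N |
|---|---|
| One-sided 5% | 100 to 102 |
| Power 85% | 144 to 146 |
| Power 90% | 170 to 172 |
| Two-sided alpha 2.5% | 154 to 156 |
| Wilcoxon, efficiency 0.955 to 0.864 | about 134 to 148 |
| ANCOVA, assumed r = 0.3 / 0.5 / 0.7 (variance factor 1 − r²) | 116 / 96 / 66 |
| Change score, d on the raw-score SD, assumed r = 0.3 / 0.4 / 0.5 (variance factor 2(1 − r)) | 176 / 152 / 126 |
| Variance inflation of 1.25 | 128 × 1.25 = 160 |

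The change-score row passes through 160 where 2(1 − r) = 1.25, that is r = 0.375 (0.363 from the unrounded normal formula). The article gives no correlation, so the r values are assumptions shown as a range. ANCOVA, the analysis named for three months under Statistical methods, moves the requirement down, away from 160.

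**The case against.** The strongest reply is that an input may have been used and not printed. The section has change-score wording: it speaks of improvement from baseline relative to control, and sets the test at "an alpha of 5% (two tailed) from pre- to post-intervention". If d was scaled to the raw-score SD and a correlation of about 0.37 assumed, 80 per arm follows. A variance inflation of 1.25 gives 160 as well. The article condenses a full protocol (version 2.0, under Trial status) that is not shown and could contain such an input. This stands as a possibility. It does not rescue the paragraph as written, which presents d, power and alpha as sufficient to produce 160. The planned three-month analysis is also ANCOVA, not a change-score test.

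A reader might infer that the 20% allowance was definitely applied twice, because 128/0.8 = 160 and 160/0.8 = 200 both match exactly. That is plausible but not established. Since 1/0.8 = 1.25, the match cannot separate a second attrition allowance from a variance factor of 1.25, and nothing in the article says which was used. For the same reason, the tempting statement that the trial enrols 40 people too many (200 against 160) holds only if no unprinted input exists.

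It can also be said that 80% is met as a minimum, since 80 per arm gives more. That is correct and bears on severity. It does not make 160 the number these inputs need.

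**Conclusion.** The printed pre-attrition figure is wrong as written. The stated inputs give 128 evaluable participants (126 by the normal approximation), against 160 printed, an excess of 25%. This rests on a 1:1 comparison of two means with d in units of the outcome SD, which is the plain reading of the section. No input stated in the article reconciles the figures, and the cause of the discrepancy cannot be determined from it.

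The error is conservative. A reader might infer from a faulty calculation that the trial is underpowered; the reverse is true. With 20% loss from 200, power at d = 0.5 is about 88%, and 80% power is reached at d of about 0.45. The mismatch does not touch the choice of endpoint, the analysis or the type I error rate. It is a reporting correction that should be made, not a defect that threatens the trial.

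**What to change.** Restate the Sample size paragraph in one of two ways, depending on what was actually done.

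1. If no further input was used: give 64 per arm (128 evaluable), or 160 enrolled after 20% attrition. Then say that the planned 200 leaves about 160 completers at 20% loss, with about 88% power at d = 0.5 or 80% power at d of about 0.45.
2. If a further input was used: state it (for example a correlation with the SD to which d refers, or a variance inflation) and show how it leads to 160.

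A rationale that was not part of the planning should not be supplied afterwards to account for the surplus. The cost is one corrected paragraph; no extra participants or procedures, and no change to the design, are needed.

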### Recruitment

Recruitment commenced in January 2022 and is ongoing. Participants are recruited from Karolinska Comprehensive Cancer Centre, Sweden using the following three methods:Nurses and physicians involved in the care of the respective diagnosis groups will inform potential participants about the trial during a regular visit or by mail/letter or telephone. Details of interested individuals will be forwarded to the research team.A nurse in the research team will review electronic patient records to identify potential participants and contact the treating nurse or physician to obtain permission to contact the individual.Information posters and brochures will be placed in the waiting rooms of the respective outpatient clinics where patients are followed up so that interested individuals can make direct contact with the research team.

Interested individuals will be provided with verbal and written information about the trial by a nursing member of the research team who will also screen for eligibility. Screening will be conducted in consultation with the trial physician in the case of any individual having a medical condition that may prevent safe participation in the study. Eligible individuals will then be provided with the full participant information form explaining the trial aims and procedures. After reading through the full information form and having the opportunity to ask questions, participants will be invited to sign a written informed consent form by a nursing member of the research team.

The personal trainers invited to participate in the focus groups or individual interviews will be provided with the full participant information form, given the opportunity to ask questions, and invited to sign a written informed consent form.

### Assignment of interventions

After the completion of baseline testing, study participants will be randomised by a member of the research team on a 1:1 basis in block samples, using the computer-generated randomisation program ALEA. Randomisation will be stratified by disease type (breast, prostate or colorectal) and treatment with chemotherapy (yes or no). Study investigators and participants will be blinded to group allocation at baseline, but not at the subsequent testing timepoints. The design is open label so unblinding will not occur.

### Data collection and management

Data are collected and entered exclusively by members of the research team. In the interest of standardising the testing procedures, a standardised operating procedures manual has been developed and all testers will undergo standardised training to conduct the tests. The same members of the research team monitor the participants to ensure follow-up completion, including email and SMS reminders. All hard copies of forms are kept in a locked filing cabinet at Karolinska Institutet. All recorded data are pseudonymised. Participants will not be identified in the resulting manuscripts and reports. Only the study investigators have access to trial information and the dataset.

The EX-MED Cancer Sweden trial is registered at www.ClinicalTrials.gov (NCT05064670). Ethical permissions have been obtained by the Swedish Ethical Review Authority (2019–04,151, 2021–01,715). All participants must provide written informed consent to participate in this trial.

### Statistical methods

Analyses will be performed using an intention-to-treat approach. For the quantitative analysis, descriptive statistics will be used to describe baseline characteristics. Analysis of covariance (ANCOVA) and linear mixed modelling will be used to detect any significant differences between the two groups at three and six months, respectively. Corresponding effect sizes will also be calculated. Explorative sub-analysis by cancer type will be conducted to investigate if any effects of the exercise intervention are cancer type specific.

For the qualitative analysis, focus group discussions/individual interviews will be transcribed verbatim and analysed using qualitative content analysis.

### Serious adverse events

All (serious) adverse events ((S)AE) related to the study measurements or exercise, reported by the participant, observed by the personal trainer or study investigators will be recorded. Participants in both groups will be asked by a study investigator about any study measurement- or exercise-related (S) AEs systematically and in a standardised manner at the 3- and 6-month testing timepoints. Additionally, participants in the intervention group will be asked by the personal trainer, before and after each exercise session, about any potentially exercise-related (S) AEs that have occurred during or between exercise sessions and will report back to the study investigators. In the event of a SAE event during the exercise sessions, the personal trainer will immediately call for medical assistance and contact the study investigators. (S) AEs are reported to the participant’s physician or nurse in a standardised manner. Participants involved in the trial are covered by the national patient insurance system.

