### Intervention

All participants will undergo baseline testing of physical fitness and strength prior to randomisation. Participants randomised to the intervention will be registered for the next exercise group to commence within 2 weeks of baseline testing. Participants will complete two 60-min distance-based exercise sessions per week for 12 weeks (24 sessions in total). The program consists of a combination of resistance and aerobic exercises. The exercise sessions are delivered by upskilled personal trainers in groups of up to eight people. Educational modules have been developed for the personal trainers and are delivered by the research group prior to delivering the intervention. These modules are the EX-MED Cancer PD course [19], developed in Australia by author PC, with modifications made to contextualise the content to the Swedish healthcare setting. Modules consist of an introduction to cancer, side effects of cancer treatments, screening and monitoring of cancer, exercise prescription for cancer and working with people with cancer. Prior to commencing the exercise intervention, participants will receive an in-person familiarisation of the exercise program from a member of the research team. They will be provided with a hard copy of the exercise program, resistance bands for training, a detailed information booklet about exercise for people with cancer, and a logbook to record attendance, exercise adherence and level of exertion. Any barriers to exercise identified by the participant or the research team will also be discussed, and solutions developed together.

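### Adverse events thought unrelated to testing or exercise are not captured in either arm, and session-by-session questioning in the exercise arm only could distort any count that pools the two sources

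*Protocol article*

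**What the plan says.** All of the recording rules stand in the section Serious adverse events of the protocol article.

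- **Scope.** What is recorded is "All (serious) adverse events ((S)AE) related to the study measurements or exercise". No section provides for recording events regardless of cause.
- **Enquiry common to both arms.** A study investigator asks every participant "about any study measurement- or exercise-related (S) AEs systematically and in a standardised manner at the 3- and 6-month testing timepoints".
- **Enquiry in the exercise arm only.** As an addition, "participants in the intervention group will be asked by the personal trainer, before and after each exercise session, about any potentially exercise-related (S) AEs". The trainer's question covers events "that have occurred during or between exercise sessions and will report back to the study investigators".

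Three other sections bear on this. Intervention sets the programme at "two 60-min distance-based exercise sessions per week for 12 weeks (24 sessions in total". Participant timeline says that controls "will have no contact with the research team until the 3-month testing session, unless initiated by the participant". Assignment of interventions says that investigators and participants know the allocation after baseline, and adds: "The design is open label so unblinding will not occur".

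**The concern.** Two stated rules shape the safety data.

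The first is the scope. If only related events are recorded, relatedness has to be settled in some way before an event counts, in a trial where everyone knows the allocation after baseline. A fall, an injury or a hospital admission thought to have nothing to do with exercise leaves no record in either arm. A mistaken attribution cannot be corrected later, because the event is not there to review. Randomisation would otherwise let harm be assessed by comparing arms, without attributing cause case by case. Related-only recording gives that up.

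The second is the intensity of questioning. The exercise arm is asked repeatedly over 12 weeks, including about what happened between sessions. Controls are first asked at month 3 and must recall about three months. Minor events have more chances of being logged in one arm than in the other.

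The article hopes that the programme will become part of standard care, so readers are likely to look at its safety data by arm.

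**Working it through.** **Inputs from the article.** Two sessions a week for 12 weeks; two trainer enquiries per session (before and after); two visit enquiries in both arms (months 3 and 6); 200 participants randomised 1:1, so 100 per arm.

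**The article's own figure.** 2 × 12 = 24 sessions, which agrees with the stated 24.

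**Scheduled enquiries per participant at full attendance.**

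| Period | Exercise arm | Control arm |
|---|---|---|
| Up to and including month 3 | 24 × 2 + 1 = 49 | 1 |
| After month 3, to month 6 | 1 | 1 |
| Total | 50 | 2 |
| Common standardised enquiry only | 2 | 2 |

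The asymmetry is 24 × 2 = 48 enquiries, all within the 12-week programme. If attendance were 80% or 60% (assumed; about 19 or 14 sessions), the exercise arm would have 19 × 2 + 2 = 40 or 14 × 2 + 2 = 30 enquiries.

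**What a pooled count could do (illustration only).** The article gives no event risk or capture rate, so these are assumptions. Let the true risk of at least one qualifying event be 20% in both arms. Let 90% of affected exercisers be captured, and 30%, 50% or 70% of affected controls. Recorded risk = true risk × capture.

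Exercise arm: 0.20 × 0.90 = 18%.

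The chance of a two-sided p < 0.05 in the direction of excess in the exercise arm, with n = 100 per arm, is approximately Φ[(Δ − 1.96 × SE0) / SE1]. Here Δ is the difference in recorded risks, SE0 = √(2 p̄(1 − p̄)/n) with p̄ the mean of the two recorded risks, and SE1 = √([p1(1 − p1) + p2(1 − p2)]/n).

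| Control capture | Recorded, control | Spurious risk ratio | Calculation | Chance of false significance |
|---|---|---|---|---|
| 30% | 6% | 18/6 = 3.0 | Φ[(0.12 − 1.96 × 0.0460)/0.0452] | 75% |
| 50% | 10% | 18/10 = 1.8 | Φ[(0.08 − 1.96 × 0.0491)/0.0487] | 37% |
| 70% | 14% | 18/14 = 1.3 | Φ[(0.04 − 1.96 × 0.0518)/0.0518] | 12% |

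The nominal rate is 5%. The table shows only that a plausible gap in capture could matter if the two sources were pooled. It does not estimate the gap in this trial.

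**The case against.** The strongest reply is that no such comparison is planned. Adverse events are not among the primary or secondary outcomes, and Statistical methods mentions no analysis of them. How sources are tabulated is usually left to the full protocol or the analysis plan, neither of which is shown. This stands: there is no contradiction, and nothing says that the two sources will be merged. It does not dispose of the scope rule, which the article states outright.

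Several stronger readings are tempting, and the text does not support them.

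- *Event rates cannot be compared at all.* Exercisers get the same standardised enquiry at months 3 and 6 as controls. That stream is symmetric, 2 against 2, and can be shown by arm if kept apart, although it covers related events only.
- *Unblinded staff filter events by a formal causality judgement before recording.* The article does not say who decides relatedness, how or when. The trainer's question extends to events that are only potentially related, which is a low threshold.
- *Controls cannot have a qualifying event.* The rule covers study measurements and exercise, not assigned exercise. Controls undergo the same tests, may be given activity advice and may take up exercise, a possibility the Discussion acknowledges.
- *Ascertainment is biased 25-fold.* The ratio 50/2 counts prompts at full attendance. Prompts before and after one session are not independent chances, and an event remembered at month 3 is captured either way.

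Session-by-session questioning is also a sensible safety measure and is not itself at fault. Finally, recruitment is under way, so a change now would leave visits on two definitions. That is a real cost.

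**Conclusion.** The point holds as a weakness of the safety data, on two counts.

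First, events thought unrelated, serious ones included, are not captured in either arm, so all-cause events cannot be shown by arm and attribution cannot be revisited. This rests on the article's stated scope. If the full protocol records all serious events elsewhere, this part falls away to that extent.

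Second, up to 48 additional enquiries per participant, confined to the 12-week programme, fall on the exercise arm alone. A count that pools both sources may therefore show an excess there through ascertainment alone. The number of enquiries follows from the article at full attendance. The spurious risk ratios of 1.3 to 3.0 depend wholly on assumed capture rates and an assumed 20% risk.

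The quality-of-life analysis at 3 months is not affected.

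**What to change.** 1. At the existing 3- and 6-month visits, ask both arms the same standard question about all serious adverse events, and about adverse events that led to health-care contact or limited activity, whatever the cause.
2. Classify relatedness after the event has been recorded, and state who does so.
3. Keep the source of each report in the data. Base any presentation by arm on the visit enquiry only.
4. Keep the trainers' session questions, and report those events separately as a description of the exercise arm.

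The change needs a reworded visit form and a reporting rule, with no new visits or staff. A few more events will have to be logged. Because recruitment is ongoing, visits before the change will have used the narrower question, so the date of change should be recorded and data from before and after it shown separately.
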